**Methods/design:**

This cluster randomised control trial will recruit 776 office-based employees from public sector organisations in Belfast and Lisburn city centres, Northern Ireland. Participants will be randomly allocated by cluster to either the Intervention Group or Control Group (waiting list control). The 6-month intervention consists of rewards (retail vouchers, based on similar principles to high street loyalty cards), feedback and other evidence-based behaviour change techniques. Sensors situated in the vicinity of participating workplaces will promote and monitor minutes of physical activity undertaken by participants. Both groups will complete all outcome measures. The primary outcome is steps per day recorded using a pedometer (Yamax Digiwalker CW-701) for 7 consecutive days at baseline, 6, 12 and 18 months. Secondary outcomes include health, mental wellbeing, quality of life, work absenteeism and presenteeism, and use of healthcare resources. Process measures will assess intervention “dose”, website usage, and intervention fidelity. An economic evaluation will be conducted from the National Health Service, employer and retailer perspective using both a cost-utility and cost-effectiveness framework. The inclusion of a discrete choice experiment will further generate values for a cost-benefit analysis. Participant focus groups will explore who the intervention worked for and why, and interviews with retailers will elucidate their views on the sustainability of a public health focused loyalty card scheme.

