The UK and US Governments [13, 14] have encouraged the use of incentives for promoting healthy lifestyles. The use of financial incentives for health-related behaviour change has been met with some scepticism [15], although their acceptability may be contingent on various factors, such as their effectiveness, type, and the target behaviour [16]. There is evidence to support the use of financial incentives for the initiation of behaviour change, for example, smoking, substance abuse [17–20]. Further, recent research has demonstrated evidence of financial incentives for single, one-off heath behaviours, such as vaccinations [19], and encouragingly, habitual health-related behaviour change [20]. However, the evidence for their effect on other health behaviours is sparse. Some financial [21] and non-financial incentives [22] have been shown to increase levels of physical activity, at least in the short-term and mainly with respect to structured exercise programmes [22], rather than free-living physical activity. There is a wealth of evidence on reinforcement of behaviour that shows that whilst incentives may be effective at changing behaviour, the effects are unlikely to be maintained when the incentives are withdrawn in the absence of other interventions [23]. Therefore, financial incentives alone may not be sufficient to promote maintained physical activity behaviour change, but may do so when embedded within an evidence-based, theoretically-driven intervention [16]. Further, financial incentive interventions designed using behavioural economic concepts have been shown to be effective for changing behaviour [24]. There is also limited evidence around the cost-effectiveness of interventions to promote physical activity in the workplace [25, 26], or indeed the cost-effectiveness of financial incentive-based interventions [19]. Therefore, to address such gaps in the evidence base and following the successful completion of a pilot study [27], we aim to conduct a cluster RCT of a complex intervention incorporating financial incentives to encourage physical activity and maintained behaviour change.

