### Outcome measures

All outcome measures will be analysed and, where required, collected by a Postdoctoral Research Fellow (PDRF) blinded to group allocation. Self-reported outcome measures will be collected at baseline, 6 months and 18 months (unless otherwise stated), via online questionnaires distributed by email and automatically collated via Qualtrics (www.Qualtrics.com) (successfully employed in our pilot trial [27]).

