#### Physical activity

The primary outcome is mean steps/day objectively measured by a sealed pedometer (to blind participants to the output) worn on the waistband (Yamax Digiwalker CW-701, Japan), for which reliability and validity has been established [39–41]. Participants will wear the pedometer for 7 consecutive days, complete a wear time diary, and the Global Physical Activity Questionnaire (GPAQ) to elucidate the context of activity undertaken [42]. These measures will be collected at baseline, 6 (immediately post-intervention), 12 (6 months post-intervention) and 18 months (1 year post-intervention). This schedule ensures that we can account for the impact of seasonality of physical activity behaviours on the intervention effect.

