#### Economic analyses

The economic evaluation will comprise a cost-effectiveness and cost-utility analysis from the public sector perspective and a cost-benefit type analysis from the employer’s perspective (Objective 3). A cost-effectiveness and cost-utility analysis will compare costs and outcomes associated with the Intervention to those associated with the Control Group at three time-points. For the initial within study analysis, the outcome measures used will be (a) changes in mean steps per day; and (b) a within study measure of QALYs determined from EQ-5D. QALYs will be adjusted for any imbalances between groups at baseline [86]. Thus, the initial analysis will present an estimate of cost-effectiveness of the intervention in terms of the incremental costs associated with increasing physical activity and a cost-utility analysis in terms of incremental costs per QALY gained. The uncertainty surrounding the estimates of cost and effects for the Intervention and Control Group will be investigated through the use of bootstrapping [87]. In a sensitivity analysis we will compare subgroups and assess the uncertainty in their incremental cost-effectiveness ratios (ICERs) by plotting the associated cost-effectiveness acceptability curves. The longer term analysis will employ a decision model, populated with reference to the literature, to link short term study outcomes to longer term impacts on health and wellbeing. The model structure will be informed by a review of other models undertaken in this area, including the modelling work undertaken for NICE (2008) [88]. Data will be embodied in the model through the specification of probability distributions for each parameter, to reflect the uncertainty. Probabilistic sensitivity analysis will be undertaken, using Monte Carlo simulation, to investigate the uncertainty surrounding the longer term estimates of costs, effects and cost-effectiveness of the intervention.

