From the public sector perspective, the analysis will involve firstly generating ICERs using healthcare utilisation data and EQ-5D data. Secondly, from the employer’s perspective, the effect of physical activity on absenteeism will be used to estimate potential cost savings to employers (absenteeism model); and thirdly, we will employ an algorithm to translate changes in EQ-5D into quantifiable changes in productivity (productivity model [89–91]). Individual EQ-5D scores at baseline, 6 and 18 months will also be converted into estimated levels of productivity using this algorithm and the total productivity gain over 6 and 18 months for each group will be calculated. To calculate the ICER, from an employer’s perspective, the additional costs will be divided by the additional gain in total employee productivity by the Intervention Group.

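### EQ-5D is not collected at the existing 12-month contact, so the QALY and productivity totals rest on an assumed utility path over the year after incentives stop

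*Protocol article*

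**What the plan says.** All of the following is in the protocol article.

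- **EQ-5D schedule.** Outcome measures sets the general rule: "Self-reported outcome measures will be collected at baseline, 6 months and 18 months (unless otherwise stated), via online questionnaires distributed by email". Health and wellbeing introduces the EQ-5D-5L and gives it no other schedule. Economic analyses repeats the same three points for the productivity conversion: "Individual EQ-5D scores at baseline, 6 and 18 months will also be converted into estimated levels of productivity using this algorithm".
- **Use of EQ-5D.** Economic analyses will "compare costs and outcomes associated with the Intervention to those associated with the Control Group at three time-points". One outcome there is "a within study measure of QALYs determined from EQ-5D", adjusted for baseline imbalance. A total productivity gain, derived from EQ-5D by an algorithm, is also planned to 6 and to 18 months.
- **Existing 12-month contact.** Physical activity says of the pedometer, wear diary and GPAQ: "These measures will be collected at baseline, 6 (immediately post-intervention), 12 (6 months post-intervention) and 18 months (1 year post-intervention".
- **End of incentives.** The abstract says: "The 6-month intervention consists of rewards (retail vouchers, based on similar principles to high street loyalty cards), feedback". Months 6 to 18 are therefore the year after the rewards stop.

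**The concern.** A QALY is a total over time, and so is a cumulative productivity gain. Each needs a value for the between-group difference at every moment of follow-up, so something has to be assumed between measurements. Here the longest gap, a full year, starts when the incentives are withdrawn. That is when the course of the effect is least certain: whether change is maintained is Objective 2 of the trial. Activity will be observed in the middle of that year, but utility will not.

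The planned uncertainty analyses do not cover this. Bootstrapping addresses sampling variation, and each resampled three-point area keeps the same assumed path. The probabilistic sensitivity analysis belongs to the longer-term decision model.

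At stake are the cost per QALY and the employer's ICER based on productivity. If incremental cost is unchanged, an error in the QALY gain moves the cost per QALY by the inverse factor.

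**Working it through.** The article gives no QALY gain, utility difference or QALY share, so there is no figure of the plan's own to reproduce. The check works in units of the 6-month difference.

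**Inputs**

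- Measurement times in years: 0, 0.5 and 1.5 (Outcome measures; Economic analyses). The additional time that is available is 1.0 (Physical activity).
- Between-group utility difference: d0 = 0, because QALYs are to be baseline-adjusted (Economic analyses); d6 > 0; d12 and d18 left free.
- Straight-line joins between measured points. This is my assumption, taken from usual area-under-the-curve practice. The article states no rule.

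**Step 1. Area from the three planned points**

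- Months 0 to 6: 0.5 × (0 + d6)/2 = 0.25·d6
- Months 6 to 18: 1.0 × (d6 + d18)/2 = 0.5·(d6 + d18)
- Total: 0.75·d6 + 0.5·d18

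**Step 2. Share of the gain from months 6 to 18**

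Share = 0.5·(d6 + d18) / (0.75·d6 + 0.5·d18)

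- d18 = 0: 0.50/0.75 = 66.7%
- d18 = 0.5·d6: 0.75/1.00 = 75%
- d18 = d6: 1.00/1.25 = 80%

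**Step 3. Area with a 12-month value added**

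0.25·d6 + 0.5·(d6 + d12)/2 + 0.5·(d12 + d18)/2 = 0.5·d6 + 0.5·d12 + 0.25·d18

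The three-point total minus this is 0.25·d6 + 0.25·d18 − 0.5·d12 = 0.5 × [(d6 + d18)/2 − d12]. The error is half a year multiplied by the distance of the 12-month difference from the midpoint of its neighbours. It is zero only if the 12-month value lies on the line, and it can take either sign.

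**Step 4. Size when d18 = 0 (three-point area 0.75·d6)**

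- Gone by 12 months: true area 0.50·d6; 0.75/0.50 = 1.5, overstated 1.5 times.
- Held in full to 12 months, then falling to zero at 18: true area 1.00·d6; 0.75/1.00 = 0.75, understated by 25%.
- Gone by 9 months: 0.25 + 0.25 × 0.5 = 0.375·d6; 0.75/0.375 = 2 times.
- Lost at once at 6 months: 0.25·d6; 0.75/0.25 = 3 times.

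A 12-month EQ-5D recovers the first two cases exactly. In the other two, the four-point area is 0.50·d6, so the overstatement falls from 2 to 0.50/0.375 = 1.33 times, and from 3 to 0.50/0.25 = 2 times.

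With fixed incremental cost, the reported cost per QALY would be 1/1.5 = 0.67 of its true value in the first case and 1/0.75 = 1.33 times its true value in the second.

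**Step 5. Sensitivity to d18**

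- d18 = 0.5·d6 (three-point total 1.00·d6): with d12 = 0 the four-point area is 0.625·d6, overstated 1.6 times. With d12 = d6 it is 1.125·d6, understated by 11%.
- d18 = d6: no error if the effect was constant in between.

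The same fractions carry over to the productivity total only so far as the conversion algorithm is close to linear in EQ-5D. The article does not give its form.

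**The case against.** The best case for leaving the plan alone has several parts.

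- **The schedule is coherent.** Baseline, end of intervention and end of follow-up is a sensible set of times for a secondary outcome, and it is stated consistently. This stands: it is a design choice and not a contradiction. It does not remove the dependence on the path, and the contact that would reduce it already exists.
- **The joining rule may be in a document not shown.** This stands, and the absence of a rule from the article is not criticised here. But any rule would be an assumption about the same gap. The missing 12-month measurement is fixed by the stated schedule.
- **Both ends of the year are measured.** This is correct. Only the path between them is unobserved, and d18 will be known. The scenarios with d18 = 0 are illustrations, not forecasts.
- **A productivity total to 6 months is also planned.** It avoids the later gap, but the 18-month total does not.

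Three stronger readings are tempting, and the document does not support them.

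- A reader might infer that the protocol expects the effect to fade, so that the cost per QALY will look too favourable. The Background sentence is conditional: "the effects are unlikely to be maintained when the incentives are withdrawn in the absence of other interventions". This intervention includes other behaviour change techniques intended to move participants towards habitual activity. Fading is not predicted, and the error can go either way.
- A reader might infer that two-thirds is the most the post-incentive year can contribute, since it is 12 of 18 months. With a baseline-adjusted difference and straight lines, two-thirds is the minimum for any non-negative 18-month difference (step 2).
- A reader might infer that the whole of Objective 3 depends on this. Cost per change in steps uses the pedometer, which is read at 12 months, and the absenteeism model uses sick leave. Neither depends on joining EQ-5D values.

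**Conclusion.** The concern holds in a limited form. Under the stated schedule, the within-study QALY and the EQ-5D-based 18-month productivity total depend on an assumed utility path across the whole post-incentive year. Given straight-line joins, a zero adjusted baseline difference and a positive 6-month difference, that year supplies 67% to 80% of the QALY gain for an 18-month effect between none and full maintenance. If the 18-month difference is zero, the error ranges from a 1.5-fold overstatement (gone by 12 months) to a 25% understatement (held to 12 months). Faster loss gives larger overstatements.

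The direction is unknown beforehand, so this is avoidable uncertainty and not a demonstrated bias. The document gives no utility difference, so it cannot be said whether a cost-effectiveness conclusion would change. The primary outcome, the steps-based cost-effectiveness analysis and the absenteeism model are untouched. The point merits a change because the remedy is small and cost-effectiveness is in the trial's title.

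**What to change.** Add the EQ-5D-5L to the existing 12-month GPAQ contact in both arms, and compute QALYs and EQ-5D-based productivity from baseline, 6, 12 and 18 months. The cost is one short questionnaire (five dimensions and a visual analogue scale) at a contact that already takes place, with slightly more participant burden.

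Where the 12-month contact has already passed, report a sensitivity analysis in which the utility gain ends at 6 months, which under the same assumptions gives 0.25·d6. This needs no new data. It bounds the result on one side only, by showing how much of the reported gain depends on the later year, and does not replace the missing measurement.

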#### Analysis of discrete choice and economic experiments (objective 8 and 9)

To analyse the revealed preferences data we will use a two-step modelling approach to explain an individual’s physical activity in relation to his/her characteristics [73, 74]. The revealed preferences data will be analysed with a Cragg’s double hurdle model [92–94] to first address physical activity participation, and then to analyse the amount of physical activity. We will run separate models for different types of physical activity (e.g. walking, gym) to produce estimates for the effect of wage, cost of physical activity and participants’ characteristics on the amount of physical activity. This model will provide us with a ‘revealed’ implicit monetary value for units of physical activity. A random utility econometric model will be fitted to the DCE data to determine the implied individual thresholds inducing behaviour change [80]. Estimation will take place in a panel specification, and Bayesian posterior estimates of threshold values will be informed by the sequence of responses. Data from the field experiment to assess time and risk preferences will be analysed using maximum likelihood estimates, allowing for within-subject clustered standard errors, as each participant answers more than one time preference choice [76]. The data collected on the amount of physical activity at baseline and after the intervention will allow us to run another Cragg’s double hurdle model for behaviour change, and explore how differences in inter-temporal preferences, baseline physical activity levels, incentives and other participant’s characteristics affect behaviour change. The Cragg’s double hurdle model will allow us to investigate the two-step process in behaviour change: firstly, relating to the decision to do more physical activity compared to baseline; secondly, the decision of how much physical activity to do.

#### Process evaluation analyses

Focus groups and semi-structured interviews will be audio-recorded and analysed using thematic content analysis [95] whereby identified themes will be represented in a matrix for further analysis and interpretation [96, 97] (Objective 7). Qualitative data will be entered into NVivo, which will be used to manage the relevant data and to explore inter-relationships between themes. Each transcript will be coded independently by two researchers. Analysis will explore implementation and receipt of rewards and contextual factors affecting these. Potential causal pathways will be explored in order to develop hypotheses relevant to secondary moderator and mediator analyses. Additionally, quantitative data from PAL scheme usage and web usage will be used in the analyses of intervention fidelity, using simple descriptive statistics. Within the context of the RE-AIM Framework, we will compare the characteristics of our trial population with the target population, to gauge the potential generalisability and impact of our results. Propensity scores will be used to compare the characteristics of trial participants with the inactive working population as a whole in Northern Ireland, using available population-level data [98]. These propensity scores will also be used as to ascertain whether a weighting method can be employed, using the scores, to generalise the results to the target population.

### Update on study progress

During the recruitment phase for the study, a revised power calculation was undertaken assuming a less demanding effect size estimate taken from the recent literature together with our actual baseline data on mean and variance of cluster size and an intra-class correlation co-efficient of 0.029. In the original protocol, the sample size calculation for the trial was determined using an anticipated effect size of d = 0.21 (based upon a previous meta-analysis of workplace based physical activity interventions). However none of the included studies were incentive-based interventions for physical activity. More recent literature has been published [99, 100], including a meta-analysis in which a mean effect size for incentive based interventions of 16 min of MVPA per day was estimated, equating to an effect size of approximately 1600 steps (d = 0.40). Additionally, in the TRIPPA study [100], which is examining the influence of financial incentives on the effectiveness of a wireless-upload pedometer to encourage weekly physical activity goals, the study was powered to detect a difference of a minimum of 30 min of MVPA per week between groups and power calculations were based on considerably higher effect size than assumed in our original protocol (0.35). Therefore, under the assumption that our original estimate was too conservative, the power calculation has been updated. For an effect size of 0.40, a study of 330 per group (or 660 in total) would have 90 % power at the 5 % significance level. Assuming a 15 % drop-out, the study would need to randomise 776 participants.

## Discussion

Given the rise in physical inactivity and associated health conditions, such as diabetes, heart diseases and cancer, worldwide, there is a growing need for scalable, effective, and affordable public health interventions. This study will provide necessary research concerning the potential effectiveness and cost-effectiveness of a novel workplace physical activity intervention and an understanding of assumed pathways of behaviour change initiation and maintenance. Further, detailed cost-effectiveness analyses will assess whether financial incentives are an appropriate use of government and private sector resources. The scope for introducing financial incentives in public health is extensive, but there is much to learn.

The study is designed to maximise the potential for roll-out in similar settings, by engaging the public sector and business community in designing and delivering the intervention. In collaboration with retail partners, an existing “proven” mechanism that delivers behaviour change in the private sector was applied to a public health setting using a sustainable “Physical Activity Loyalty Card.” We have developed a sustainable business model using a ‘points’ based loyalty platform, whereby local businesses ‘sponsor’ the incentive (retail vouchers) in return for increased footfall to their business, which is aligned to precepts of the Department of Health Public Health Responsibility Deal [13]. For financial incentive schemes to be worthwhile in the longer term, they must be based on a sustainable model. The UK Government and the U.S. government have encouraged those involved in public health to work collaboratively with business. This study provides an example of how researchers can successfully engage with the business sector in public health.

## Abbreviations

BCTs, behaviour change techniques; BMI, body mass index; DCE, discrete choice experiment; EQ-5D-5 L, euro-Qol 5 dimension 5 level questionnaire; FFQ, food frequency questionnaire; GIS, geographical information systems; GPAQ, global physical activity questionnaire; ICER, incremental cost-effective ratio; Km, kilometres; m, metres; MICE, missing imputation by chain equations; MRC, medical research council; MVPA, moderate-vigorous physical activity; NHS, national health service; NICE, national institute for health and care excellence; NIHR, national institute for health research; PAL, physical activity loyalty; QALY, quality adjusted life year; RCT, randomised controlled trial; RE-AIM, reach, effectiveness, adoption, implementation, maintenance; SD, standard deviation; SEP, socio-economic position; SF-8, short form-8; SPIRIT, standard protocol items: recommendations for intervention trials; TRIPPA, trial of economic incentives to promote physical activity; UK, United Kingdom; US, United States; WEMWBS, Warwick Edinburgh mental wellbeing scale; WHO, World health organisation; WTA, willingness to accept; WTP, willingness to pay
